**Figure 2 F2:**
[figure not shown]
**Schedule for the intervention day.** *R1 is the researcher who gives general instructions and distributes participants in each session. R2 is the researcher who gives information about walking to all participants and applies the control intervention. R3 is the researcher who applies the motivational intervention. R4 is the researcher who applies the implementation intention intervention and is blinded to participants’ previous experiment condition (motivational or neutral). **MIG: Motivation and implementation intention group; IG: Implementation intention group; CG: Control group.

#### Motivational intervention

The aim of the motivational intervention is to ensure strong behavioral intention. The TPB
[24] establishes that the behavioral intention (that is, the readiness to perform a specific behavior) is determined by the person’s attitude toward the behavior (the positive or negative global evaluation of performing the specific behavior), the subjective norm (the social pressure perception of engaging in the behavior or not) and the perceived behavioral control (the perception that the behavior is under the person’s control). Attitudes, subjective norms and perceived behavioral control are explained, respectively, by behavioral beliefs, normative beliefs and control beliefs (Figure 
3).

**Figure 3 F3:**
[figure not shown]
Schematic illustrating the Theory of Planned Behavior.

In the TPB, beliefs represent the substantive information available to guide people’s decisions with regard to their behavioral performance. Thus, we will target a modification of participants’ beliefs in order to achieve a change with regard to the intention. The motivational intervention will be designed to produce changes in the behavioral, normative or control beliefs associated with the predictors of the behavioral intention (stage 2 of phase I of the research). With regard to the physical exercise behavior, attitude and control perception have been found to be the main predictors of the intention to engage in exercise
[25-27]. However, the TPB establishes that the relative weight of each predictor (and consequently the targeted beliefs) changes if the specific behavior changes. In fact, with regard to walking, the control perception has more weight than attitudes
[16]. This situation could differ in people with a chronic health problem such as FM. Therefore, it is necessary to explore the particular predictive relationships between the targeted walking behavior and the specific population
[24].

A specific proposal for a brief intervention based on the TPB for interventions on walking was recently published
[44]. The authors propose several steps for the intervention, such as the identification of the target constructs, the elicitation of key salient beliefs underpinning these constructs and the selection of appropriate behavior change techniques. We followed these recommendations, and phase I (stage 2) of the study is focused on the identification of the target constructs and the salient beliefs through an exploration of the TPB predictors of walking behavior. The beliefs associated with these predictors will be used to enhance intention by implementing writing and imagery techniques. Strategies such as a graded activity will be implemented
[45] as soon as we establish the role of pain, FM impact and fear of movement on the behavioral intention in the whole group.

#### Volitive intervention: implementation intentions

Implementation intentions are “if–then” plans that specify when, where and how a goal will be achieved, linking a critical situation (the “if” component) with a goal-directed behavior (the “then” component)
[28]. Implementation intentions are hierarchically subordinated to goal intentions (in this study, the behavioral intention). Implementation intentions have been shown to have a moderate to strong effect on goal attainment
[46].

We expect participants in the MIG and IG groups to be able to use their plans to adjust their walking activity to the circumstances they have foreseen and specified. We will focus these plans on the management of the inhibitors of the walking behavior, which we will have previously identified in stage 2 of phase I (control beliefs). As has been shown in previous research
[47,48], participants can regulate their emotional responses through attentional implementation intentions (for example, to ignore some stimuli) or by specifying their desired behavioral and emotional responses (for example, to be calm or relaxed). Participants form their plans individually, and, in order to facilitate the internalization and memorization of these plans, they will be requested to write the specific implementation intentions on a sheet of paper and place it in a visible location at home. A copy of the sheet will be given to the research team so that the team can perform the follow-up on the specific goals. This will be the last intervention of the day, and the researcher who conducts this session will ask participants to carry on with the task until they finish.

### Measures

#### Phase I (first year)

In the first year of the study, measurements of physical activity, walking behavior, TPB variables, fear of movement, pain, FM impact and emotional status will be taken. All questionnaires will be self-administered by the participants. A summary of variables and schedules in this phase is shown in Table 
2.

**Table 2 T2:** **Measures taken and schedule during phase I**^
**a**
^

**Variables**	**Instrument**	**Schedule**^ **b** ^		
			**Stage 2**	
		**Stage 1**	**Time 1**	**Time 2 (week 7)**
Walking behavior				
Walking pattern	*Ad hoc* self-report scale	X	X	X
	Daily logs			X
Minutes spent walking in previous week	IPAQ walking	X	X	
Steps and distance	Pedometer			X
TPB variables	*Ad hoc* TPB questionnaire			
Behavioral intention			X	
Attitude			X	
Perceived norm			X	
Perceived behavioral control			X	
Behavioral beliefs			X	X^c^
Injunctive and descriptive beliefs			X	X^c^
Control beliefs			X	X^c^
Fear avoidance	Spanish adaptation of TSK		X	
Total physical activity	IPAQ–Spanish Short Form	X	X	
Intense physical activity		X	X	
Moderate physical activity		X	X	
Sitting		X	X	
Fibromyalgia impact	Spanish adaptation of FIQ		X	
Pain intensity	11-points numerical rating scale	X	X	
Emotional status: Distress	Spanish adaptation of HADS		X	

^a^FIQ: Fibromyalgia Impact Questionnaire; HADS: Hospital Anxiety and Depression Scale; IPAQ: International Physical Activity Questionnaire; TPB: Theory of Planned Behavior; TSK: Tampa Scale for Kinesiophobia. ^b^Women who attended the association or university laboratory for assessment. Daily logs and pedometer readings were taken at time 1. ^c^For test–retest reliability.

##### Behavioral variables

To assess for behavioral variables, we will gather participants’ self-reported information as outlined below.

1. *Spanish version of the International Physical Activity Questionnaire–Short Form (IPAQ-S)*[49]: The IPAQ-S is an instrument designed to assess physical activity among adults. It can be used as a tool in intervention studies, although it was not designed for this purpose. There is a lack of self-report measures of physical activity designed for FM patients. In addition, the results obtained from well-established instruments in general populations are not good enough in FM patients
[50]. However, the IPAQ-S was previously found to be better than other physical activity instruments in identifying sedentary patients with chronic fatigue syndrome
[51]. We have chosen to use the IPAQ-S because of its Spanish translation; its short form, which is an advantage for our first mailed survey and for the FM population; and because it includes walking as a type of physical activity. The IPAQ-S allows respondents to record their sitting, walking, moderate-intensity and vigorous activities in minutes per week and calculate a total physical activity score. We will use the median minutes per week for each activity for assessment purposes. The rules for cleaning and correcting data will be applied
[49]. In this phase, we will use the IPAQ-S to characterize our reference and study populations.

2. *Behaviors*: We will use four measures to assess walking behavior. First, we will use a self-report scale to assess the usual walking pattern to identify the study population. The scale consists of six questions designed to assess whether participants usually walk for physical exercise, how many minutes they walk daily, how many days per week they walk, how many consecutive weeks they walked, whether they took rests during walking and whether they had been advised to walk by their doctor.

Second, we selected the walking score from the IPAQ-S
[49] because it refers to the previous week of the assessment. It can thus provide a more accurate measurement than our general measures because of its proximity in time and because it can limit the influence of the participant’s memory.

Third, we have designed weekly and daily logs to assess walking behavior over the course of 6 consecutive weeks. Daily logs include the days and minutes of walking and the duration of rest during the activity. In addition, participants score the perceived intensity of the activity using the Borg Rating of Perceived Exertion scale
[52]. Participants will use a pedometer (3D USB Pedometer PDM-2608) to record the number of steps and distance covered over the same period.

These measures will be used to explore the agreement between subjective and objective measurements. We need to establish this agreement because the entire study population will use daily logs, but only half of them will use pedometers.

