### Description of the overall project

The study consists of two phases, both based on the same population.

Phase I, conducted over the course of 1 year, is a cross-sectional study with two measurement stages and the following three aims:

1. We will seek to gain access to the reference population, identify the eligible population, select the study population and identify the prevalence of our selected walking criteria (stage 1). The results of stage 1 are included in this paper.

2. We will seek to identify the predictors of the behavioral intention to carry out the selected walking program using the TPB and exploring the role of pain, impact of FM and fear of movement (stage 2).

3. We will seek to explore the concordance of walking behavior measurements (subjective and objective measures) (stage 2).

Phase II, which will be conducted over the course of 2 years, is an experimental, randomized, triple-blind study with two treatment groups and one active control group. Longitudinal measures will be taken at baseline and at 7 weeks, 3 months and 9 months of postexperimental intervention. One group will receive a motivational plus implementation intentions intervention (MIG), a second group will receive only an implementation intention intervention (IG) and the control group (CG) will be given a neutral task related to postural hygiene. The three groups will receive the same information on the benefits of physical exercise in FM. Motivational intervention will be based on the predictors of behavioral intention as measured and identified in phase I (stage 2) in order to create or strengthen the behavioral intention during the experimental study.

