### Study population and recruitment process

The fibromyalgia associations of Alicante (ADEFA), Elche (AFEFE), Madrid (AFIBROM) and Talavera de la Reina (AFIBROTAR) collectively comprise a total of 2,438 members with a clinical diagnosis of FM (75.8% diagnosed by rheumatologists, 9.2% by general practitioners, 5.3% by traumatologists, 2.2% by clinical rehabilitation specialists, 0.7% by neurologists and 6.7% by clinicians in other specialties). Slightly more than half (51.4%) of the sample are receiving psychological treatment because of FM. To select our reference population (women between 18 and 70 years of age who meet the London Fibromyalgia Epidemiology Study Screening Questionnaire criteria for fibromyalgia (London-4) ), we first used the associations’ records to select the members who met the two first criteria (*n* = 2,227). We then sent letters to these 2,227 women with information about the study, together with informed consent forms, the London Fibromyalgia Epidemiology Study Screening Questionnaire
[34,35] and other questionnaires covering the remaining variables related to the sample characteristics and participation criteria. As we do not have a second clinical diagnosis confirmation, the London-4 criteria were used to ensure population homogeneity. Although these criteria screen only for widespread musculoskeletal pain and do not take into consideration other clinical aspects of FM, they give an optimal sensitivity (100%) in FM screening population studies and good positive predictive values for women in rheumatology settings
[35].

A total of 972 questionnaires (43.5%) were returned in two runs. The eligibility criteria were then applied, and our selected reference population subsequently consisted of 920 members with FM (44 did not fit the London-4 criteria and 8 questionnaires did not contain enough data). The remaining criteria were that the individual did not walk or the walking pattern did not comply with one or more features of the selected walking program, the individual was without comorbidity which impeded walking or, if there was comorbidity, the individual had received medical advice to walk. A total of 582 members (63.3%) satisfied these criteria. Figure 
1 is a flowchart of the participant recruitment process.

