#### Phase II (second and third years)

A summary of variables and the schedule of phase II is given in Table 
3.

**Table 3 T3:** **Measures and schedule of phase II**^
**a**
^

	**Instrument**	**Schedule**			
**Outcomes**		**Baseline**	**Week 7**	**Week 20 (3 months)**	**Week 43 (9 months)**
*Primary*					
Walking pattern	*Ad hoc* self-report scale	X	X	X	X
	Daily logs		X	X	X
Steps and distance	Pedometer^b^		X	X	X
*Secondary*					
Total physical activity	IPAQ	X	X	X	X
Intense physical activity		X	X	X	X
Moderate physical activity		X	X	X	X
Walking		X	X	X	X
Sitting		X	X	X	X
Physical function	Six-Minute Walk Test	X	X	X	X
FM Impact	FIQ	X	X	X	X
Pain intensity	*Ad hoc* scale	X	X	X	X
Emotional status: Distress	HADS	X	X	X	X
*Mediators*					
Behavioral intention^c^	TPB items	X	X	X	X
Implementation intentions^c^	*Ad hoc* items		X	X	X

^a^FIQ: Fibromyalgia Impact Questionnaire; HADS: Hospital Anxiety and Depression Scale; IPAQ: International Physical Activity Questionnaire; TPB: Theory of Planned Behavior. ^b^Limit of recording is 60 days. ^c^Also measured at the end of the intervention sessions.

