#### Primary outcome measures

Two primary outcomes will be assessed as indicators of each intervention’s effect on exercise adherence:

1. We will measure the proportion of participants who perform the full minimum walking criteria (at least 30 minutes in bouts of 15 minutes with a small rest between bouts, twice times weekly over a minimum of 6 consecutive weeks) at the end of the 6-week period and the proportion of participants who have maintained it at 3 and 9 months. The expected efficacy of MIG is 30% higher than CG and 10% higher than IG.

2. Among participants who perform the full minimum walking criteria, we will focus on the proportion who reach the recommended pattern for FM patients at week 6 (between two and four times weekly for about 50 minutes in bouts of 15 to 20 minutes over a minimum of 6 consecutive weeks)
[31].

We will use the same self-reported measurements of the behavior from phase I (*ad hoc* self-reported items and daily logs) and pedometer readings.

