It is important to underline that as soon as the final 274 participants agree to participate, strategies to avoid having participants dropping out will be implemented. In that sense, we will contact the 180 women who failed to attend the evaluation session but did not refuse to participate in the study. Because the participants belong to FM associations which conduct other activities for their members, we may have problems with the masking process. Participants might talk among themselves about the activities performed in each intervention group. However, nobody knows which intervention group is expected to be more successful. Participants will sign a commitment of confidentiality, and, furthermore, we will also assess the shaping of implementation intentions in the control group.

In spite of these limitations, the study addresses an important need: the enhancement of self-management in the treatment of FM. It focuses on increasing adherence to a strategy which has been shown to be effective (physical exercise, specifically walking). Furthermore, the results are expected to show the effectiveness of a short intervention which is easily applicable with a minimum of training and cost and that can be incorporated into routine clinical practice.

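### Walking eligibility is set once by mailed form in year 1 and is not stated to be re-applied at the phase II baseline, so women who already meet primary outcome 1 at that point count as successes in every arm

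*Protocol article*

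**What the plan says.** **Who is eligible.** Under Study population and recruitment process, the screen was postal: "We then sent letters to these 2,227 women with information about the study". A woman qualified on walking if "the individual did not walk or the walking pattern did not comply with one or more features of the selected walking program", so someone who walked but missed a single feature was eligible. Behavioral variables (Phase I measures) names the instrument: "First, we will use a self-report scale to assess the usual walking pattern to identify the study population". One of its six questions asks for the number of consecutive weeks walked.

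**When the trial happens.** Description of the overall project states: "The study consists of two phases, both based on the same population". Phase I takes one year, and phase II occupies the second and third years. No second selection on walking is described between them.

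**What is measured again.** Table 3 lists "Walking pattern" on the ad hoc self-report scale at the phase II baseline. The Phase II part of Statistical analysis uses the baseline walking pattern in three ways: to check randomization, as a candidate confounder, and as an effect modifier. Adjustment is conditional on association with arm, association with the outcome in controls, and a change of more than 10% in the odds ratio.

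**What is counted.** Primary outcome measures: "We will measure the proportion of participants who perform the full minimum walking criteria" at the end of six weeks, then the proportion maintaining them at 3 and 9 months. Nothing restricts this to women who failed the criteria at baseline. Sample size calculation, however, plans on rises in prevalence relative to baseline (10% control, 20% IG, 40% MIG), and the Phase II analysis text speaks of acquiring the pattern.

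**The concern.** The planned effect is about starting to walk, but the outcome is attained status. The two agree only if nobody meets the minimum criteria at the phase II baseline, and nothing in the article secures that. A woman who complied with everything except six consecutive weeks when she filled in the mailed form becomes a complier simply by continuing. No effect of the study procedures is needed.

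A woman who already complies cannot show acquisition. If she carries on, she is a success wherever she was allocated. All arms then show higher success rates, the differences shrink, power falls, and the result no longer answers whether the intervention gets non-walkers walking. The comparison of MIG with IG, on which the main hypothesis partly rests, is the more exposed because its planned margin is smaller.

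**Working it through.** **Inputs from the protocol article**
- Planned rates: 10% control (CG), 20% IG, 40% MIG; alpha 5%, taken as two-sided (Sample size calculation).
- Women who attended the first evaluation session: 274 (Phase I results). Three equal arms give 274/3 = 91.3 per arm, before any later loss.
- Timing: enrolment from May 2012, completion by the end of June 2014 (Trial status), last visit at week 43 (Table 3).

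**Assumptions**
- The article gives no share s of women who already comply at the phase II baseline. I take 10% to 30%.
- Those women stay compliant in every arm.
- The planned rates apply to the remaining women.
- The MIG-IG margin is the 20 points implied by the sample-size section. Primary outcome measures gives 10 points for the same contrast, which would leave less power throughout.

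**Plan's own figure.** There is none for this point. The 115 per group in the sample-size section does not follow from the stated contrasts: at two-sided 5% and 80% power they need 199 (10% v 20%), 32 (10% v 40%) and 82 (20% v 40%). That is a separate matter, and nothing below depends on it.

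**Age of the screening status.** 30 June 2014 minus 43 weeks is 2 September 2013. If the mailing dates from May 2012, the status could be up to about 16 months old for the last women treated.

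**Dilution.** An arm's rate p becomes p' = s + (1 - s)p. The difference between arms A and B becomes (1 - s)(pA - pB).

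**Power.** Phi[(d - 1.96 x se0)/se1], with se0 = sqrt(2 x pbar x (1 - pbar)/n) and se1 = sqrt([p1(1 - p1) + p2(1 - p2)]/n).

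Example, s = 10%, MIG v IG:
- p' = 0.10 + 0.90 x 0.20 = 0.28 and 0.10 + 0.90 x 0.40 = 0.46, so d = 0.18 and pbar = 0.37.
- With n = 91.3, se0 = 0.0715 and se1 = 0.0702.
- (0.18 - 1.96 x 0.0715)/0.0702 = 0.57, so power is 72%.

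| s | MIG v IG, all women | Power | MIG v IG, baseline non-compliers only (n per arm) | Power | MIG v CG, all women | Power |
|---|---|---|---|---|---|---|
| 0 | 40% v 20% | 84% | 91.3 | 84% | 40% v 10% | over 99% |
| 10% | 46% v 28% | 72% | 82.2 | 80% | 46% v 19% | 98% |
| 20% | 52% v 36% | 59% | 73.1 | 76% | 52% v 28% | 92% |
| 30% | 58% v 44% | 47% | 63.9 | 70% | 58% v 37% | 82% |

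Restricting the analysis costs women, n(1 - s), but restores the planned 40% v 20%. On these assumptions that is the better trade at every s above zero.

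**Does the planned adjustment deal with it?** Confounders are screened first on association with arm. Randomization tends to balance baseline compliance, so it will usually fail that screen and stay out of the model. Whether or not it enters, the outcome still counts these women as successes.

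**The case against.** **No re-check is stated, but a condensed article may omit one.** This is fair as to operational detail, and the full protocol may contain such a check. What stands is the text given: the outcome definition, applied as written, counts baseline compliers, and the stated uses of the baseline scale do not include confirming eligibility.

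**Baseline walking is not ignored.** It heads the list of potential confounders and is tested as an effect modifier, and the Discussion openly expects some participants who walk. So mixed baseline walking is partly handled and disclosed. But the adjustment is conditional, and an effect-modifier test does not define what the main analysis estimates.

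**The share and its persistence are assumed.** Correct. The article itself stresses poor adherence, and an intervention might help women who already walk to continue. The loss would then be smaller, but the estimate would mix acquisition with maintenance.

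**Stronger readings that the article does not support**
- *Bias between arms.* Randomization spreads prior compliers across the arms, so no spurious advantage follows.
- *Six weeks of stage 2 logging turns women into walkers.* The article describes logs ("we have designed weekly and daily logs to assess walking behavior over the course of 6 consecutive weeks") but nowhere says that they change behaviour.
- *Late entrants differ because they skip stage 2.* The Discussion says "we will contact the 180 women who failed to attend the evaluation session but did not refuse to participate in the study", which is compatible with bringing them into that same assessment.
- *The diluted control rate contradicts the planned 10%.* The 10% is an increase, not an attained level. On the plan's own scale the control increase moves only from 10 to between 9 and 7 points.

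**Conclusion.** The point holds as one of dilution and an unclear target of estimation. Eligibility on walking is fixed from the year 1 mailing, is not stated to be re-applied in years 2-3, and outcome 1 does not depend on baseline status although the planned effect is a change from baseline. For s between 10% and 30%, every contrast shrinks by that share, and the planned 20-point MIG-IG difference becomes 18 to 14 points. The fall in MIG-IG power is material, while the MIG-CG comparison remains adequately powered across the range. These figures rest on the assumed s, on full persistence in all arms, on the planned rates, and on about 91 women per arm with no later loss. The change should be made, but the trial's validity does not turn on it.

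**What to change.** In Primary outcome measures and in the Phase II part of Statistical analysis:

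1. Define the acquisition analysis of outcome 1 at the week 7 measurement in women who do not meet the full minimum criteria on the phase II baseline scale.
2. Decide this from pre-intervention data only, by one rule for all arms, applied by staff blinded to allocation. The Randomization section reports the 449 women as already allocated, so the restriction falls after allocation and needs these safeguards. For the same reason, the existing arms cannot now be balanced on stage 2 completion.
3. Report women already compliant at baseline separately, for maintenance.
4. As a sensitivity analysis, analyse all randomised women with baseline compliance as a fixed covariate, not subject to the confounder screen.

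Cost: wording only, since the scale is already scheduled at that visit. The downside is a somewhat smaller main analysis set, about 82 to 64 per arm for s = 10% to 30%, in a sample where 274 attended against the 345 planned before the dropout allowance.
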